## Abstract

Backgrounds: Social cognition is defined as the mental operations underlying social behavior. Patients with schizophrenia elicit impairments of social cognition, which is linked to poor real-world functional outcomes. In a previous study, transcranial direct current stimulation (tDCS) improved emotional recognition, a domain of social cognition, in patients with schizophrenia. However, since social cognition was only minimally improved by tDCS when administered on frontal brain areas, investigations on the effect of tDCS on other cortical sites more directly related to social cognition are needed. Therefore, we present a study protocol to determine whether multi-session tDCS on superior temporal sulcus (STS) would improve social cognition deficits of schizophrenia. Methods: This is an open-label, single-arm trial, whose objective is to investigate the efficacy and safety of multi-session tDCS over the left STS to improve social cognition in patients with schizophrenia. The primary outcome measure will be the Social Cognition Screening Questionnaire. Neurocognition, functional capacity, and psychotic symptoms will also be evaluated by the Brief Assessment of Cognition in Schizophrenia, UCSD Performance-Based Skills Assessment-Brief, and Positive and Negative Syndrome Scale, respectively. Data will be collected at baseline, and 4 weeks after the end of intervention. If social cognition is improved in patients with schizophrenia by tDCS based on this protocol, we may plan randomized controlled trial.

## 1. Introduction

The prevalence of schizophrenia is about 0.7% [1], with positive, negative, mood symptoms, and cognitive dysfunction. The first episode appears after adolescence and follows a chronic course with repeated remission and exacerbation of psychotic symptoms. In this process, cognitive and social function decline [2,3,4]. As a result, 70% of chronic patients are reported to be unable to find employment [5,6].

Cognitive dysfunction is one of the core symptoms of schizophrenia and exists from the early stage of onset to the chronic stage [7]. Several domains of neurocognition, such as learning memory, working memory, executive functioning, verbal fluency, and attention/information processing, are known to be impaired in schizophrenia [7]. Similarly, it has been noted in recent years that social cognition [8], i.e., mental operations underlying social behavior, is also impaired in schizophrenia. Social cognition consists of the domains of emotion recognition, social perception, theory of mind (ToM), and attributional bias [9], whose neural basis differs from that of neurocognition [10]. Moreover, it has been reported that improvement of social cognition is directly linked to improvement of social function, whereas there is argument that the association between neurocognition and social function is mediated by social cognitive function [11]. Therefore, in recent years, the importance of developing treatments for social cognition has been discussed.

The neural substrates of social cognition may include the orbitofrontal cortex, medial prefrontal cortex (mPFC), superior temporal sulcus (STS), and amygdala; these brain regions show a decrease in functional connectivity in schizophrenia [12]. Among these sites, the amygdala is involved in emotion recognition [13], while the prefrontal cortex governs ToM [14]. On the other hand, the STS is considered to play a role in both domains of social cognition [15] (see Table 1 [12,13,14,15,16,17,18,19]).

Neuromodulation is a method of changing nerve activity by applying electrical stimulation or the other agents to a specific nerve site in the body. Neuromodulation ranges from noninvasive approaches, such as transcranial magnetic stimulation, to invasive (implanted) approaches, such as spinal cord stimulation and deep brain stimulation [20]. Among them, transcranial direct current stimulation (tDCS) is a safe, inexpensive, and feasible neuromodulation that modifies nerve activity by providing a weak current of 1–2 mA for about 5–30 min/session [21]. The therapeutic effects of tDCS are thought to be mediated by promotion of cortical excitability through anodal stimulation [22]. In addition, enhanced excitatory synaptic transmission via anodal tDCS may promote glutamate transmissions, and suppress gamma-aminobutyric acid transmissions in the cortex. Moreover, it positively or negatively modulates the activities of dopamine, serotonin, and acetylcholine transmissions in the central nervous system. These neural events may change the balance between excitatory and inhibitory inputs [22,23]. With these mechanisms, tDCS has been suggested to ameliorate symptoms of several psychiatric disorders, e.g., major depressive disorder and schizophrenia.

tDCS has been shown to improve several domains of neurocognitive function, especially working memory, in schizophrenia [24]. On the other hand, only two studies have been conducted to determine the ability of tDCS to improve social cognitive disturbances of schizophrenia [25,26]. So far, only one study reported small facilitative effects of tDCS on emotion recognition with the left dorsolateral prefrontal cortex (DLPFC) as the target site in schizophrenia [25]. It should be noted that these studies used anodal stimulation on the frontal areas, i.e., the left DLPFC [26]. As social cognition may be governed mainly by other brain regions, e.g., the STS [12,13,14,15,16,17,18,19], it is hypothesized that anodal stimulation over this cortical area would be advantageous for treating social cognition disturbances.

These considerations prompt us to determine whether stimulation of skull surface above the STS, e.g., T3 or T4 (mid-temporal) of the International 10–20 electroencephalography system, would enhance social cognition in patients with schizophrenia. Moreover, intervention in the STS may affect hallucinations, as the STS is adjacent to the superior temporal gyrus (STG), and the network of cortical areas containing STGs is involved in hallucinations [27]. Therefore, we present a study protocol for an open-label, single-arm trial designed to evaluate the efficacy and safety of tDCS on the left STS. To our knowledge, this is the first attempt to administer tDCS targeting the STS in patients with schizophrenia.

## 2. Study Protocol

### 2.1. Trial Design

This study investigates the efficacy and safety of multi-session tDCS over the left STS to improve social cognition for patients with schizophrenia. This is a single-center trial at National Center of Neurology and Psychiatry, Tokyo, Japan. An open-label, single-arm study will be conducted on 15 participants with a diagnosis of schizophrenia based on the Diagnostic and Statistical Manual of Mental Disorders (DSM-5). We selected an open-label, single-arm design, because there is no precedent for tDCS over the left STS, and the major focus of this study is to verify the tolerability and safety of tDCS over the STS. Participants will receive 10 sessions of active tDCS in 5 consecutive days (twice per day) (see Figure 1). The study design is in accordance with the 2013 Standard Protocol Items: Recommendations for Interventional Trials (SPIRIT) Statement (Table S1) [28]. This study was registered within the Japan Registry of Clinical Trials (Trial ID: jRCTs032180026).

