### 2.4. Sample Size Calculation

Total study sample sizes of *n* = 15 have been recommended by our previous study [29], assuming an estimated mean UCSD Performance-based Skills Assessment-brief (UPSA-B) difference from baseline to follow-up of 10.6, with a standard deviation of 15.5. Under these conditions, the power of the primary analysis was 0.8, so approximately *n* = 13 was estimated (one-sample Student’s t-test). Therefore, it was decided to include a total of 15 samples, taking into account the dropouts of the study.

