#### 2.6.1. Cognition

The primary outcome is scores on the Social Cognition Screening Questionnaire (SCSQ) [30], which includes test of attributional style, and theory of mind (ToM). To evaluate ToM more accurately, we will also use False Belief Task [31], Hinting Task [32], and Autism-Spectrum Quotient (AQ) [33]. To evaluate emotion recognition, we will use the Facial Emotion Selection Test (FEST) [34]. To provide a standard metric for combining test scores into domains and comparing performance over time, Brief Assessment of Cognition in Schizophrenia (BACS) scores will be converted to z-scores, which shows performance relative to healthy people [35]. The premorbid IQ will be also estimated using the Japanese Adult Reading Test (JART) [36] (see Table 3).

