### 2.7. Data Collection and Data Management

The assessments will be conducted at baseline and 4 weeks after the end of the last stimulation (Table 2). All evaluations will be conducted by experienced psychologists. The data will initially be recorded in a paper file and each participant will be assigned a code number. These files will be stored in a locked security box. After the follow-up data are collected, all data in the paper files will be transcribed to the Electronic Data Capture system (HOPE eACReSS; Fujitsu, Tokyo, Japan), which is a secure system designed for storage of personal and patient data. The data will be sent to independent data managers to assess whether the data are collected properly, focusing on the status of consent acquisition, eligibility of participants, evaluation items, and confirmation of drop-out/terminated cases. These data managers will also oversee and review the progress of the trial. If a participant withdraws their consent, they will be dismissed from the study. At the same time, we will record the dropout rate, and the number of people with adverse events requiring treatment. We will define a dropout rate of less than 10% as a safety criterion and perform a quantitative assessment of safety. The Efficacy and Safety Assessment Committee, whose members are independent of the research and come from the National Center of Neurology and Psychiatry, will check and assess whether the trial is conducted safely and properly, and will also decide whether to stop the trial if any severe adverse events or protocol violations occur. In addition, an on-site data monitor will conduct monitoring to ensure the trial is performed properly, data is properly recorded, and data reliability is ensured. If we conduct any necessary protocol modifications, we will report them to the Clinical Research Review Board, and to the Ministry of Health, Labor and Welfare for registration in the Japan Registry of Clinical Trials website (https://jrct.niph.go.jp).

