### 2.8. Statistical Analysis

Correlations between baseline values and their changes from baseline of SCSQ, Hinting Task, FEST, BACS, UPSA-B, and PANSS scores, will be evaluated. Correlations will be examined for chlorpromazine equivalent dose of antipsychotics vs. changes from baseline of SCSQ, Hinting Task, FEST, BACS, UPSA-B, and PANSS scores. Correlations will also be examined for the change of UPSA-B scores from baseline and changes of the corresponding scores from baseline.

Statistical analysis will be conducted using STATA 14, created by StataCorp in TX, USA. For continuous variables in the SCSQ, Hinting Task, FEST, BACS, UPSA-B, and PANSS, we will use Student’s t-test. Pearson’s product moment correlation coefficient will be used for the relationship between clinical variables.

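### Safety is the stated major focus, but the only numeric criterion for judging it is dropout below 10%, which ignores treated adverse events and carries no interval

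*Protocol article*

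**What the plan says.** All references are to the protocol article.

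- **Purpose.** Section 2.1 gives two reasons for having no control arm: this stimulation site has no precedent, and "the major focus of this study is to verify the tolerability and safety of tDCS over the STS". The size is fixed there too: "An open-label, single-arm study will be conducted on 15 participants".
- **Safety data.** Section 2.6.4, under Outcomes, defines adverse events and three grades. Mild events need no therapeutic intervention, moderate events need one, and serious events need inpatient treatment. It also requires checks around each session and stops the whole study after severe events in two patients. Table 2 schedules adverse events at every time point.
- **Safety criterion.** Section 2.7, on data management, states that "we will record the dropout rate, and the number of people with adverse events requiring treatment". It then sets dropout below 10% as the safety criterion and promises a quantitative assessment of safety.
- **Outcomes and analysis.** The primary outcome is SCSQ (2.6.1, Table 3). Table 3 has no safety or tolerability row. Section 2.8 plans a t-test "For continuous variables in the SCSQ, Hinting Task, FEST, BACS, UPSA-B, and PANSS", and correlations. The sample size in 2.4 rests on a UPSA-B "difference from baseline to follow-up of 10.6, with a standard deviation of 15.5".

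**The concern.** An uncontrolled pre-post comparison says little about efficacy, and 2.6 itself concedes unblinded assessors and a possible learning effect. What such a trial can report directly is how many patients tolerate the course and how many need treatment for an adverse event. The plan records both counts but ties a numeric criterion only to dropout.

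Two consequences follow. First, the criterion can be met while the adverse event record is poor, because patients can be treated for an adverse event and still finish. Second, it is read off a point estimate in 15 patients. Meeting it could then be reported as safety having been verified, when the data exclude only high rates.

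**Working it through.** **What set the sample size.** The standardised effect is d = 10.6 / 15.5 = 0.684. Section 2.4 gives power 0.8 and a one-sample t-test but no alpha; I assume 5%.

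- One-sided, normal approximation: n = ((1.645 + 0.842) / 0.684)² = 13.2, which matches the stated figure of about 13.
- Two-sided: 16.8, which does not match.

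So 13 reproduces under a one-sided 5% test and was raised to 15 for dropouts. For this point it matters only that 15 came from a functional-capacity score and not from any precision target for safety.

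**What the criterion means.** 10% of 15 is 1.5. One dropout is 6.7% and meets the criterion; two are 13.3% and fail it.

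**What it does not see.** Suppose at most one patient drops out. The criterion is then met whether none of the 15 or all of them had a moderate adverse event that needed treatment. If severe in the stopping rule means serious as graded in 2.6.4 (an assumption, since the two words are not linked there), moderate events do not trigger that rule either.

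**How well it discriminates.** The probability of meeting it is P(X ≤ 1), with X binomial (15, p). The true rates are assumed, as the article gives none.

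| True dropout rate | P(criterion met) |
|---|---|
| 5% | 0.83 |
| 10% | 0.55 |
| 15% | 0.32 |
| 20% | 0.17 |

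**Precision for any proportion.** These are exact (Clopper-Pearson) two-sided 95% intervals with 15 patients. For zero events the upper limit is 1 − 0.025^(1/15) = 0.218.

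| Events | Observed | 95% interval |
|---|---|---|
| 0/15 | 0% | 0 to 21.8% |
| 1/15 | 6.7% | 0.2 to 31.9% |
| 2/15 | 13.3% | 1.7 to 40.5% |

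If only 13 patients were treated, zero events would leave rates up to 24.7% open. Both results that meet the dropout criterion (0/15 and 1/15) have upper limits well above 10%.

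**Chance of seeing nothing.** The probability of no event in 15 is (1 − p)^15. At an assumed true rate of 10% it is 0.9^15 = 0.206. At 5% it is 0.46 and at 1% it is 0.86 (the complements of 0.54 and 0.14 for at least one event). Excluding a 10% rate with zero events needs ln 0.05 / ln 0.9 = 28.4, so 29 patients, at one-sided 95%.

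**The case against.** The strongest reply is that safety is well specified. A reader of Table 3 and 2.8 might infer that the trial has no safety endpoint. The documents do not support that: 2.6.4 sits under Outcomes with definitions, grades and a stopping rule, Table 2 collects adverse events throughout, and 2.7 sets a numeric criterion. Dropout is also a legitimate tolerability measure.

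Other parts of the reply stand as well:

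- This is a journal article. How adverse events are tabulated and in which analysis set may be in the full protocol or analysis plan, so a missing Table 3 row or sentence in 2.8 would not by itself be a finding.
- The treated-event count is mentioned just before the promised quantitative assessment and may feed it. Serious and nonserious events also go into the reports to the Review Board (section 3).
- An efficacy primary outcome does not contradict the aims, because the abstract, introduction and 2.1 state efficacy and safety jointly.
- Any first study of this size gives wide intervals, and the article claims no excluded event rate.

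A reader might also infer that 2.4 and 2.7 contradict each other, since raising 13 to 15 allows for two dropouts and two would fail the criterion. A cautious allowance may exceed an acceptability threshold, so I do not rest the point on this.

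What the reply does not answer is that the one numeric criterion stated for judging safety is insensitive to treated adverse events and is a point-estimate rule. That is a matter of what the article fixes, not of what it leaves out.

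**Conclusion.** The concern holds in a limited form. Safety is measured and monitored, but the criterion by which it will be judged is a retention rule (at most 1 of 15) that takes no account of treated adverse events and carries no interval. It also does not appear among the listed outcomes or in the analysis section. With 15 patients, zero events excludes only rates above about 22%, and one event is compatible with rates up to 31.9%. The verb in 2.1 therefore promises more than the trial can deliver.

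The interval figures assume that all 15 patients are treated and counted; fewer would widen them. The discrimination figures depend on assumed true rates of 5 to 20%. The blindness of the criterion to treated events depends on neither. The change should be made, because it alters what the trial can conclude about its stated focus.

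**What to change.** - In Table 3, name two main safety and tolerability outcomes: the proportion of patients with at least one adverse event requiring treatment (moderate or serious as graded in 2.6.4), and the proportion dropping out or not completing the course.
- In 2.8, report both with exact 95% intervals among all treated patients, next to the existing dropout criterion.
- State the period over which adverse events count. Section 2.6.4 defines them as occurring during stimulation, while Table 2 also collects them at follow-up.
- In 2.1, replace *verify* with *describe* or *preliminarily assess*, and state that zero events in 15 excludes only rates above about 22%.
- Keep SCSQ as the primary efficacy outcome.

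The cost is small. Adverse events, the treatment given and dropout are already recorded. Completion of all 10 sessions is not explicitly listed as recorded and may need one added item. The downside is a more modest safety claim.

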### 2.2. Participants

Inpatients or outpatients treated at National Center Hospital, National Center of Neurology and Psychiatry will be enrolled. Participants will be recruited by referrals from treating psychiatrists. Those psychiatrists will not have any conflicts of interest with the outcomes of this trial. The principal investigator must provide written informed consent before starting the trial. After providing the informed consent, participants will be screened by a treating psychiatrist to establish whether they meet the eligibility criteria. Participants will be given a gift certificate worth JPY 3000 per day as a reimbursement, and a gift certificate worth JPY 21000 in a total of 7 days including each tDCS session, and baseline/follow-up evaluation.

### 2.3. Inclusion and Exclusion Criteria

Participants must meet the following inclusion criteria:(1)Diagnosed as schizophrenia in DSM-5.(2)Aged between 20 and 70.(3)Being able to understand the objectives and content of the study, and provide consent to participate in it. (The ability to consent to participate in this study will be considered insufficient, when patients’ Intelligence Quotient (IQ) is less than 70, or they present with acute psychiatric symptoms. Those patients will be provided with necessary medical care separately from this trial.)(4)Having Social Cognition Screening Questionnaire (SCSQ) scores of less than 34 points. Therefore, participants whose scores are 34 or more will be excluded from this study.

Patients with any of the following conditions will be excluded from the study:(1)Present or past history of severe organic lesions in the brain, dementia, or epilepsy.(2)With alcohol or substance use disorder that was present within 12 months from screening.(3)Contraindicated against electro convulsive therapy or tDCS, e.g., severe cardiovascular diseases, such as myocardial infarction, or aneurysms at high risk of rupture.(4)Were treated with tDCS or other neuromodulations within the past 2 months. (We will ask whether participants have any history of tDCS or other neuromodulations.)(5)Deemed inappropriate to participate judged by the principal investigator, e.g., when participants’ psychiatric symptoms are unstable.

The dose of psychotropic drugs will not be changed during the study period. Cognitive rehabilitation will not be performed during the period. Therefore, we will exclude patients who are scheduled for cognitive rehabilitation.

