### 2.6. Outcomes

Patients receive a psychological evaluation, including a screening evaluation, after being briefed on the purpose of the study and agreeing to participate in the study. Psychological assessment data will be collected at baseline and 4 weeks after the final stimulus (see Table 2). Baseline and follow-up evaluations will be performed by experienced psychologists who are not blinded. Although the interval between the baseline and follow-up evaluation is more than 5 weeks, which secures adequate washout period, the leaning effect of psychological evaluation will be a possible limitation.

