**Figure 2 jpm-11-00317-f002:**
[figure not shown]
Placement map for the intervention. tDCS montage will place the anode in the left superior temporal sulcus (STS) and the cathode in the contralateral supraorbital region, which corresponds to the T3 (mid-temporal) and FP2 (front-polar) regions in the International 10–20 electroencephalography system.

**Table 1 jpm-11-00317-t001:** Neural basis of social cognition [12,13,14,15,16,17,18,19].

Domains of Social Cognition	Neural Basis
Emotion recognition	Amygdala, superior temporal sulcus, medial prefrontal cortex, inferior occipital gyrus, etc.
Theory of mind (ToM)	Superior temporal sulcus, medial prefrontal cortex, middle temporal gyrus, etc.
Attributional bias	Orbitofrontal cortex, insular cortex, striatum, amygdala, superior temporal sulcus, etc.

**Table 2 jpm-11-00317-t002:** Study schedules.

	Study Period				
	Baseline	Intervention			Follow-Up
**Time point**	Within 2 weeks before the start of intervention	Day 1	Days 2–4	Day 5	4 weeks after the end of the last stimulation

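### Patients are selected for a low SCSQ and that same score appears to be the baseline of the single-arm primary test, so the expected change is positive even with no treatment effect

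*Protocol article*

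**What the plan says.** Section 2.3 makes the Social Cognition Screening Questionnaire an entry criterion: "Having Social Cognition Screening Questionnaire (SCSQ) scores of less than 34 points", and "participants whose scores are 34 or more will be excluded from this study". Section 2.6.1 and Table 3 name the same questionnaire as the primary outcome.

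Section 2.6 describes one pre-treatment evaluation ("Patients receive a psychological evaluation, including a screening evaluation") and two measurement times: "Psychological assessment data will be collected at baseline and 4 weeks after the final stimulus". Table 2 has a single pre-treatment column, headed "Within 2 weeks before the start of intervention", which holds both the eligibility screen and the only SCSQ before stimulation.

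The trial is open-label and single-arm with 15 participants (section 2.1). Section 2.8 assigns Student's t-test "For continuous variables in the SCSQ, Hinting Task, FEST, BACS, UPSA-B, and PANSS". Section 2.4 calls the test one-sample when it sizes the trial on a baseline-to-follow-up difference. The only retest artefact acknowledged is the learning effect (section 2.6). The abstract says what may follow: "If social cognition is improved in patients with schizophrenia by tDCS based on this protocol, we may plan randomized controlled trial".

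**The concern.** A score measured with error, when used to select patients from one side, is on average too low in those selected. On retest their mean moves back towards the mean of the group they came from. If the selecting score is also the baseline, this shift enters the change score in full. With no control arm, nothing subtracts it. A t-test of the mean change against zero then attributes regression to the mean to stimulation.

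At stake is the reading of the declared primary outcome. The estimated SCSQ gain is biased towards benefit, and the test rejects more often than its nominal level when there is no effect. A practice gain pushes the same way, so the two artefacts add.

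**Working it through.** **Does one score serve both purposes?** Table 2 places the eligibility screen and the only pre-treatment SCSQ in one column, and section 2.6 includes screening in the same evaluation. Section 2.2 fits this: JPY 21000 / JPY 3000 = 7 paid days, which is 5 stimulation days + 1 baseline + 1 follow-up. No separate screening SCSQ is described.

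**Which test?** The plan's own figure helps here, although it concerns UPSA-B and not SCSQ. With mean change 10.6 and SD 15.5, d = 10.6/15.5 = 0.684. The normal approximation at 80% power gives:

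- one-sided 5%: ((1.645 + 0.842)/0.684)² = 13.2, close to the stated 13;
- two-sided 5%: ((1.960 + 0.842)/0.684)² = 16.8.

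So the stated size fits a one-sample test of change against zero, and fits it only as a one-sided test. Neither alpha nor sidedness is stated. I use two-sided 5% as the main case (2.5% in the improvement tail) and show one-sided 5% beside it.

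**Expected change with no effect.** Assumptions: baseline and follow-up are bivariate normal in the referred population with the same mean m and SD s, retest correlation ρ, no treatment effect and no practice gain. With k = (34 − m)/s,

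expected change = (1 − ρ) × s × φ(k)/Φ(k).

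The document gives neither m, s nor ρ, nor the share of referred patients below 34. I therefore vary the share excluded, 1 − Φ(k). At ρ = 0.7 and half excluded, k = 0 and φ/Φ = 0.3989/0.5 = 0.798, so the shift is 0.3 × 0.798 = 0.24 SD. The SD of change is then 0.737, the standard error for n = 15 is 0.737/√15 = 0.190, and the expected t is about 0.239/0.190 = 1.26 where zero is intended.

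**False-positive rate.** Simulated with n = 15, 200,000 null trials per setting, ρ = 0.7:

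| Share excluded by the cutoff | φ(k)/Φ(k) | Spurious gain (SD) | Significant gain, two-sided 5% (nominal 2.5%) | Significant gain, one-sided 5% |
|---|---|---|---|---|
| 10% | 0.195 | 0.06 | 4.5% | 8.6% |
| 20% | 0.350 | 0.11 | 7.2% | 12.7% |
| 50% | 0.798 | 0.24 | 21.5% | 32.6% |
| 70% | 1.159 | 0.35 | 40.5% | 54.3% |

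**Dependence on ρ** (two-sided 5%). At 50% excluded, ρ = 0.5 gives 0.5 × 0.798 = 0.40 SD and 35%; ρ = 0.9 gives 0.1 × 0.798 = 0.08 SD and 10%. At 10% excluded, the same two correlations give 0.10 SD and 5%, and 0.02 SD and 4%.

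**How well would a regression-based correction do?** A Mee-Chua type test regresses follow-up on baseline minus the screened mean and tests the intercept against that mean. With the screened mean treated as known, n = 15 and ρ = 0.7, it holds 2.5%. Its power for a true 0.5 SD effect is about 31% at 50% excluded and 16% at 70% excluded, because it must extrapolate to or beyond the edge of the enrolled scores. It leaves practice effects in: with an assumed practice gain of 0.2 SD and no treatment effect, it is significant in about 14%, 8% and 6% of trials at 20%, 50% and 70% excluded.

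**The case against.** The strongest reply is that the size is unknown. If nearly all referred patients score below 34, the bias is close to negligible: 0.06 SD and 4.5% at 10% excluded with ρ = 0.7. That stands. The direction follows from the document; the magnitude does not.

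A reader might infer that regression to the mean by itself will produce a positive trial. The figures do not support that. Even at 50% excluded and ρ = 0.7, about 78% of null trials show no significant gain. The gain is there in expectation, not in every trial.

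A reader might also infer that a go decision hangs on this test. The abstract says only that a randomised trial may be planned and gives no threshold. Section 2.1 puts the major focus on tolerability and safety, and the only numeric criterion is the dropout rate in section 2.7. A later controlled trial would itself remove the bias. This limits the consequence. It does not remove it: efficacy is a stated objective, SCSQ is the declared primary outcome, and its improvement is the stated reason for a possible next trial.

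Finally, some premises are inferred. The null of zero is not written out, the term one-sample appears only in the sample-size section, and Table 2 gives the eligibility screen its own row. A separate screening SCSQ in the full protocol is possible, but nothing in the article points to one. Nor is this a detail left to an analysis plan: the article itself fixes the criterion, the schedule and the type of test.

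**Conclusion.** The concern holds in this form: as the article is written, the primary SCSQ change has a positive expectation with no treatment effect, and a significant gain is more likely than its nominal level. At n = 15 and retest correlation 0.7 the spurious gain runs from about 0.06 to 0.35 SD and the false-positive rate from about 5% to 41% as the share excluded runs from 10% to 70%. These figures rest on bivariate normality, the assumed correlation, an assumed share excluded and a two-sided 5% test. A one-sided 5% test gives higher rates, against a nominal 5%. The direction is firm, given that the eligibility score is the baseline. The document does not establish that a false-positive result is likely, or that a formal decision depends on it.

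**What to change.** 1. Keep the SCSQ score of every screened patient, including those at 34 or above, and report the share excluded.
2. Beside the unadjusted change, report the change minus the expected regression shift, (1 − ρ) × s × φ(k)/Φ(k), with m and s taken from all screened patients and ρ varied from 0.5 to 0.9. A Mee-Chua type estimate may be added as a sensitivity analysis, but conclusions should not rest on it alone.
3. State that a significant unadjusted SCSQ change will not be read as evidence of efficacy, or as the basis for planning a randomised trial, unless it exceeds the expected shift.
4. Read it alongside the Hinting Task, False Belief Task and FEST, which Table 2 already collects at both times and which were not used for selection.
5. Name regression to the mean with the learning effect as a limitation in section 2.6.

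The cost is analysis wording and the retention of scores already obtained at screening. The downsides are a smaller apparent effect and a wider interval (considerably wider for the Mee-Chua estimate when many are excluded), and dependence on an assumed retest correlation and an estimated screened mean. Practice effects remain uncorrected.
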